***Weight***

Children will be weighed without shoes and wearing light clothes, standing still in the middle of the platform of the scale without touching anything. Body weight will be equally distributed on both feet. Weights will be taken by a registered nutritionist using a (Seca solar scale model 0213). The Seca solar scale will be calibrated against an electronic scale. Weight measurements will be taken twice, and the average will be calculated. Weight will be recorded to the nearest 0.1 kg (Lee and Nieman, 2010). A solar scale will be used because some pre-schools do not have electricity and **Appendix B** will be used for recording.

***Height***

Height will be measured using a stadiometer (Seca model 0123). The participants will be barefoot, standing with heels close together, arms to side, legs straight and knees together, looking straight ahead and wearing minimal clothing. The participants will stand with shoulders relaxed and looking straight ahead. Heels, buttocks, scapular (shoulder blade) and back of the head will be against the vertical surface in a Frankfurt position (Lee and Nieman, 2010). Height measurements will be taken twice, and the average will be calculated. Height will be recorded in centimetres to the nearest 0.1 cm (Lee and Nieman, 2010) (**see Appendix B**) for recording.

***Mid Upper Arm Circumference***

[figure not shown]

***Figure 4: MUAC measuring tape.***

The MUAC is the circumference of the left upper arm that is measured at the mid-point between the tips of the shoulder and elbow. The participant’s left arm will be bent then the researcher will find and mark the mid-point between the two marks. There arm will be hanging straight down, and a MUAC tape will be wrapped around the arm at the midpoint mark. The MUAC will be measured to the nearest 1m (**see Appendix B**) for recording.

1. ***Dietary intake and patterns***

A one day 24-hour recall will be used to collect detailed information about all foods and beverages consumed using the multiple pass method (Steinfeldt *et al*., 2013). Foods will have been consumed in the past 24 hours, most commonly, from midnight to midnight the previous day (**see Appendix C)**. Six daily intervals will be included, namely: breakfast (period up to 09h00), In-between snack (between 09h00 and 12h00), lunch (12h00 to 14h00), In-between snack (14h00 to 18h00), dinner (18h00 to 20h00), and after dinner (after 20h00). Guardian/parents will provide this information. A FFQ will be used to establish food consumption patterns including the *Cucurbita moschata* seeds. A selected pictorial FFQ will be designed for the children to establish if they know and consume the seeds (**see Appendix D**). Preschool menu will also be evaluated at this stage using the 24 hr recall form for recording at least once a week during the implementation of the intervention.

1. ***Biochemical measurements***

Zinc status will be determined by serum zinc concentrations and iron status via haemoglobin, serum ferritin, transferrin receptor and C- reactive protein (CRP) among pre-school children using flame atomic absorption spectrophotometer. The anthropometric status of the preschool children will be assessed by measuring weight and height to calculate the body mass index (BMI).

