**3.6.3.5. Monitoring and quality control**

Plate wastage and consumption adherence will be monitored and recorded by trained field workers. Monitoring for plate wastage and adherence will be done each day randomly. In order to assess the plate wastage and adherence on the consumption of *Cucurbita moschata* seeds **Appendix E** will be used for recording. Trained field workers will record amount given and remaining after feeding on randomly selected children, ten each time, they will be expected to do this twice a week. To assess the consumption of other iron and zinc rich foods, the parents/caregivers will be requested to fill out a food dairy to record for food consumed by their children at home. A food diary will be given to parents/caregivers to record food that is been given to children at home. This will help to monitor the compliance on the consumption of iron and zinc rich food. They will be asked to fill one day per week covering all seven-week days over 6 months (**see Appendix F)**. Sensory evaluation will be done once a month in the experimental preschools by the researcher at the preschool site.

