**3.6.3.6. Data analysis**

A record of consumption will be kept on whether the children did consume mashed *Cucurbita moschata* flesh mixed with grounded *Cucurbita moschata* seeds and will be recorded in frequencies taking into consideration the wastage. Plate wastage observations will be quantified from the adherence record and plate wastage studies. Thematic analysis will be used to synthesize and interpret the observed data. Frequencies will also be used for food patterns analyses from the food diary using SPSS version 24 or latest.

A short quiz with two questions on the importance of the *Cucurbita moschata* seeds will be created to test the effectiveness of the song. The researcher conducts the quiz at the end of the six months with the children and analyse the findings.

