**3.6.4.4. Measurements, procedures and analysis**

The following measurements will be done: demographic and environmental factors, anthropometrics, dietary intakes and patterns, and biochemical data. Same parameters and procedures, which were done at the baseline and described in section 3.6.2.4, will be followed. Data will be analysed using same procedures as described for baseline, with addition regression and ANOVA to measure changes from baseline to post intervention, and between experimental and control. See table 3.5 below. This is done to determine the changes in nutritional status that is likely to have occurred because of the intervention. A statistician will be consulted.

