**Table 3.5: Proposed data analysis table**

| **Descriptive Statistics** | **Categorical data** | **Numerical data** | |
| --- | --- | --- | --- |
|  |  | **Normally distributed** | **Non-normally distributed** |
| ***Socio demographic information***   - Age - Gender   ***Anthropometric measures***   - Weight, height, MUAC - Categorization according to Z-scores: height for age, weight for age and BMI for age   ***Nutrient intake from 24hr recall***   - Total intake, - Consumption pattern   ***Dietary patterns***  Frequency of inclusion of food item in the FFQ  Morbidity diary  **Biochemical measures**   - Serum zinc - haemoglobin - Serum Ferritin - C-reactive protein - Transferrin saturation - Serum ferritin | Frequencies n (%) | Mean $\pm$ SD | Median and IQR |
| ***Analytical statistics-*** |  |  |  |
| ***Comparison of micronutrient status by subject characteristics*** | Pearson’s Chi-square test/Fishers exact test | ANOVA/T-test | Kruskal-Wallis/Mann-Whitney U tests |
| ***Association between dietary intakes and micronutrient status*** | Regression analyses with dietary intakes and anthropometric indices as dependent variables and all other as independent | | |
| ***Validation of dietary intake and micronutrient status against the intervention*** | Spearman’s correlation coefficient  Comparison of means/means Weighted kappa statistic for agreement testing  Bland Altman plots for bias and agreement testing | | |

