**APPENDIX C: 24-hour recall**

| **Section: Dietary Patterns and Intakes of children** |
| --- |

**Please describe the foods (meals and snacks) that you ate yesterday during the day and night, whether at home or outside the home. Start with the first food eaten in the morning**

*Write down all food and drinks mentioned by the respondent. When the respondent has finished probe for meals and snacks not mentioned*

| **Meal** | **Time of meal** | **Food item description** |
| --- | --- | --- |
| **Breakfast** |  |  |
| **Snack** |  |  |
| **Lunch** |  |  |
| **Snack** |  |  |
| **Dinner** |  |  |
| **Snack** |  |  |

**[Household level: consider foods eaten by the child, and exclude foods purchased and eaten outside of the home or at the preschool]**

*When the respondent recall is complete, fill in the food groups based on the information recorded above. For any food groups not mentioned, ask the respondent if a food item from this group was consumed.*

| Question  number | Food group | Examples | Yes = 1  No = 0 |
| --- | --- | --- | --- |
|  | CEREALS | corn/maize, rice, wheat, sorghum, millet or any other grains or foods made from these (e.g. bread, noodles, porridge or other grain products) + *insert local foods e.g.* *ugali, nshima, porridge or pastes or other locally* *available grains* |  |
|  | VITAMIN A RICH VEGETABLES AND TUBERS | pumpkin, carrots, squash, or sweet potatoes that are orange inside + *other locally available vitamin-A rich* *vegetables (e.g. red sweet pepper)* |  |
|  | WHITE TUBERS AND ROOTS | white potatoes, white yams, white cassava, or other foods made from roots |  |
|  | DARK GREEN LEAFY VEGETABLES | dark green/leafy vegetables, including wild ones + *locally available vitamin-A rich leaves such as amaranth, cassava leaves, kale, spinach etc.* |  |
|  | OTHER VEGETABLES | other vegetables (e.g. tomato, onion, eggplant),  including wild vegetables |  |
|  | VITAMIN A RICH FRUITS | ripe mangoes, cantaloupe, apricots (fresh or dried), ripe papaya, dried peaches + *other locally available vitamin* *A-rich fruits* |  |
|  | OTHER FRUITS | other fruits, including wild fruits |  |
|  | ORGAN MEAT (IRON RICH) | liver, kidney, heart or other organ meats or blood-based foods |  |
|  | FLESH MEATS | beef, pork, lamb, goat, rabbit, wild game, chicken, duck, or other birds |  |
|  | EGGS | chicken, duck, guinea hen or any other egg |  |
|  | FISH | fresh or dried fish or shellfish |  |

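### The 24-hour recall is meant to cover everything the child consumed, but its form tells the interviewer to leave out preschool food, including the lunch at which the trial food is served

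*Protocol*

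**What the plan says.** Section 3.6.2.5 (Dietary intake and patterns) describes the instrument: "A one day 24-hour recall will be used to collect detailed information about all foods and beverages consumed". It runs from midnight to midnight, is answered by parents or guardians, and is split into six intervals, one of which is lunch. Section 3.6.4.4 repeats it after the feeding period: "Same parameters and procedures, which were done at the baseline". Table 3.5 lists total nutrient intake under the 24-hour recall. The dietary patterns paragraph of the phase two analysis derives the dietary diversity score from it.

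Appendix C is the form. Its opening prompt asks for food "that you ate yesterday during the day and night, whether at home or outside the home". The bracketed instruction below the grid is labelled as household level but refers to food eaten by the child, and tells the interviewer to "exclude foods purchased and eaten outside of the home or at the preschool". The intervention text in section 3.6.3 has the trial food eaten at the preschool, at lunch, twice a week.

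Three other diet records exist. A food frequency questionnaire is completed at both surveys. The menu is recorded separately: "Preschool menu will also be evaluated at this stage using the 24 hr recall form for recording at least once a week". Caregivers keep a home diary: "They will be asked to fill one day per week covering all seven-week days over 6 months"; section 3.6.3.6 says of it: "Frequencies will also be used for food patterns analyses from the food diary". Table 3.5 also plans an analysis headed "Association between dietary intakes and micronutrient status", with dietary intake as a dependent variable.

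**The concern.** The text and the form define different quantities. One is the child's whole intake on the recalled day. The other is that intake minus what was eaten at the preschool and elsewhere outside the home. An interviewer holding Appendix C has two opposing instructions on one page, and field teams may resolve them differently from one preschool to the next.

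If the exclusion is followed, the missing part is not random. It is the preschool part of the day, where the trial food is served. Total intake and dietary diversity would be understated on preschool days but not on days at home, so the size of the error would also depend on the weekday on which a school happens to be visited. Chapter six of the planned dissertation (section 3.11) is to report the seeds' contribution to nutrient intake, and this record would not contain them.

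A lesser concern is that one day per survey is a noisy measure of a child's usual diet when it is related to that child's zinc or iron status.

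**Working it through.** **1. The texts side by side**

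| Place | Food eaten at the preschool |
|---|---|
| Section 3.6.2.5 | included (all foods; lunch is a listed interval) |
| Appendix C, opening prompt | included (home or outside the home) |
| Appendix C, bracketed instruction | excluded |
| Table 3.5 | needs it (total intake) |
| Section 3.11, chapter six | needs it (contribution of the seeds) |

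Four places require preschool food and one removes it.

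**2. Direction and size of the bias.** Let p be the share of a preschool day's intake eaten at the preschool. Under the exclusion, recorded intake = (1 − p) × true intake, so the understatement is p. The documents give no value for p. The diversity score counts food groups: a group eaten only at the preschool is lost, and a group also eaten at home is kept. The score can therefore fall but not rise.

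**3. Trial food.** None is served before baseline, so the baseline recall can lose ordinary preschool meals only. In the repeat recall, trial food could appear only if the recalled day is a serving day, and the exclusion removes it even then.

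**4. One day as a measure of usual intake.** Inputs from the protocol:
- Recall days per survey: k = 1.
- Diary days: 180/7 = 25.7, about 26, by section 3.6.3.5; 4 × 6 = 24 by Appendix F.
- Sample size (section 3.4), which reproduces: 40291/(1 + 40291 × 0.05²) = 40291/101.7275 = 396; plus 10% = 436.

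Assumptions, not in the documents: within-to-between-child variance ratio R of 1 to 4; true diet–status correlation of 0.20 or 0.30; two-sided 5% test; clustering ignored.

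Reliability of a k-day mean = 1/(1 + R/k). Observed correlation = true correlation × √reliability. Power is by the Fisher z approximation at n = 396.

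| | R = 1 | R = 2 | R = 4 |
|---|---|---|---|
| Reliability, 1 day | 0.50 | 0.33 | 0.20 |
| Correlation factor, 1 day | 0.71 | 0.58 | 0.45 |
| Power, true r 0.30, 1 day | 0.99 | 0.93 | 0.76 |
| Power, true r 0.20, 1 day | 0.81 | 0.63 | 0.43 |
| Correlation factor, 26 days (home food only) | 0.98 | 0.96 | 0.93 |

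With 24 days the last row is 0.98, 0.96 and 0.93 as well.

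**5. Slope.** In a simulation of 2 million draws with a true standardised slope of 0.20 and R = 1, 2 and 4:
- Diet as dependent variable, as Table 3.5 writes it: slope 0.20, 0.20, 0.20.
- Diet as independent variable: slope 0.10, 0.07, 0.04.
- Correlation: 0.14, 0.12, 0.09 either way.

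**The case against.** The bracket is labelled household level, the opening prompt includes food outside the home, and a later row of Appendix C asks at individual level about eating outside the home. The preschool menu is recorded separately, and the trial food has its own adherence and plate-waste records. On this view little is lost. Part of that stands: the form contradicts itself rather than giving one clear wrong instruction. But the bracket names the child as its subject and the preschool as an exclusion. The menu record is not described as a record per child, and plate waste is observed on ten randomly selected children at a time. Neither completes the individual child's recalled day as the plan is written.

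A reader might go further and infer that each child's diet rests on a single recall, that the diet–status association is therefore heavily diluted, and that the diary days should replace the recall. The documents do not support this, for four reasons.
- The food frequency questionnaire is a second diet measure, and the recall is itself repeated after the trial.
- Table 3.5 makes diet the dependent variable, so random day-to-day error costs precision and does not shrink that slope.
- How strong the dilution is depends on assumed values. At a true correlation of 0.30, the planned 396 children still give power of 0.99, 0.93 and 0.76 with one day.
- Appendix F asks only about food eaten at home. The high 26-day reliability is thus for home food, and the diary shares the very gap criticised here. It is also a grid filled in by caregivers, whereas the recall is a probed multiple-pass interview.

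How diary days are summarised may also properly be left to a statistical analysis plan.

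**Conclusion.** The contradiction is real and should be resolved before fieldwork. Followed literally, Appendix C makes the recall a partial record: preschool-day intake is understated by the share eaten there, dietary diversity can only be lowered, and the seeds' contribution to intake cannot be estimated from it. The direction is certain. The size cannot be stated, because the documents do not give the preschool share.

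The single recall day is a secondary limitation. It multiplies correlations with micronutrient status by about 0.71 to 0.45 for assumed variance ratios of 1 to 4, and it lowers precision, without biasing the Table 3.5 slope. Its effect on power is small to substantial, depending on the assumed ratio and true correlation.

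Both points concern dietary description and the observational diet–status association. The randomised comparison of zinc and iron status does not depend on the recall and is not affected.

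**What to change.** 1. In Appendix C, remove the preschool and outside-home exclusion from the child's recall, so that the form agrees with its own prompt and with section 3.6.2.5.
2. Complete the preschool part of the recalled day from the preschool menu record, because parents may not know what was eaten there. The menu is now to be recorded at least weekly, so it must also be taken for the recalled day at both surveys. Note on the form whether that day was a preschool day and whether a study dish was served. A menu shows what was offered rather than what the child ate, and this should be stated as a limit.
3. Optionally, add the 24 to 26 diary days as a supplementary analysis of home food only, not as a substitute for total intake, and reconcile the day count between section 3.6.3.5 and Appendix F.

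The first change costs one line. The second adds a little recording at each preschool. The third needs data entry from forms that are already to be collected, and would have to allow for uneven completion between caregivers.

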***Blood collection***

The children will be given single-dose of albendazole (400 mg) or mebendazole (500 mg) for deworming at this phase. A phlebotomist will collect 5ml blood samples from the participants. The participant’s skin will be cleaned with cotton wool and 70% alcohol at the site of the antecubital vein and the participants’ arm will be restricted with a tourniquet for < 1 minute. A trace element-free, siliconized 23-G needle will be inserted into an antecubital vein, and 5ml blood drawn into two trace element-free evacuated tubes. These will be centrifuged at room temperature for 10 min at 2000 × g and divided into aliquots to separate serum from the blood at the preschool site. Serum will be transferred into new tubes for storage in a cooler box with crushed ice prior to being frozen at −20°C until further analysed. Analysis will be conducted subsequently at Ampath laboratories in Polokwane, South Africa. routine quality control measures will be employed.

**Zinc parameter analysis (provided by Ampath)**

A 125I-radioimmunoassay (Ramco Laboratories, Inc., Stafford, TX, USA) will be used for the quantitative determination of zinc in serum.

**Iron parameter analysis (provided by Ampath)**

The following blood constituents will be analysed: haemoglobin, serum ferritin, C-reactive protein and transferrin saturation.

***Haemoglobin***

A full blood count will be used to evaluate overall health and detect a wide range of disorders, including anemia and infection in preschool children. Purple (Lavender) tube which will be used for full blood count. About 1ml of blood is sufficient to do a full blood count.

***Serum Ferritin***

Ferritin will be assed is a two–site immunoenzymatic (“sandwich”) assay (Ramco Laboratories, Inc., Stafford, TX, USA). A blood sample will be added to a reaction vessel with goat anti-ferritin-alkaline conjugate, and paramagnetic particles coated with goat anti-mouse: mouse anti-ferritin complexes. The Access Ferritin assay is a two-site immunoenzymatic (sandwich) assay. A sample will be added to a reaction vessel with goat anti-ferritin-alkaline phosphate conjugate, and paramagnetic particles coated with goat anti-mouse: mouse anti-ferritin complexes. Serum or plasma (heparin) ferritin binds to the immobilized monoclonal anti-ferritin on the solid phase, while the goat anti-ferritin enzyme conjugate reacts with different antigenic sites on the ferritin molecules. After incubation in a reaction vessel, materials bound to the solid phase will be held in a magnetic field while unbound materials are washed away. Then, the chemiluminescent substrate Lumi-Phos 530 will be added to the vessel and light generated by the reaction will be measured with a luminometer (Ramco Laboratories, Inc., Stafford, TX, USA). The light production is directly proportional to the concentration of ferritin in the sample. The amount of analytic will be the sample will be determined from a sorted, multi-point calibration curve.

***C-reactive protein and transferrin***

The C-reactive protein and transferrin will be assessed with the SYNCHRON LX® System(s), UniCel® DxC 600/800 System(s) and SYNCHRON® Systems CAL 5 Plus respectively (Human Biochemical and Diagnostic Laboratories, South Africa). CRP and transferrin reagents will be used to measure C-reactive protein and Transferrin concentration by a turbidimetric method (Ramco Laboratories, Inc., Stafford, TX, USA).

***Transferrin saturation***

TRFN reagent is used to measure the TRFN concentration by a turbidimetric method.1,2 In the reaction, TRFN combines with specific antibody to form insoluble antigen-antibody complexes. The SYNCHRON® System(s) automatically dilutes sample and dispenses the appropriate sample and reagent volumes into a cuvette. The ratio used is one-part diluted sample to 37.5 parts reagent. The system monitors the change in absorbance at 340 nanometers. This change in absorbance is proportional to the concentration of transferrin in the sample and is used by the System to calculate and express the transferrin concentration based upon a single-point calibration.

1. ***Tools and specific procedures: Record sheet.***

Data will be collected using a record information sheet for demographic data, environmental parameters, recent food intake, dietary intake, anthropometrics, and biochemical parameters. The record sheet will be developed, and pilot tested to check for anything that could impede the instrument's ability to collect data in economical and systematic fashion.

1. ***Validity and Reliability***

The validity of a measurement instrument is the extent to which the instrument measures what it is supposed to measure. Furthermore, reliability is the consistency with which a measuring instrument yields results with repeated measurements, preferably more than 10 repeats. Both validity and reliability, then, reflect the degree to which we may have errors in our measurements (Leedy and Ormrod, 2010). To ensure validity, the measurements for anthropometry will be taken twice and the average will be calculated, and the developed questionnaire and intervention will be piloted and pre-tested before data collection.

To ensure reliability, the developed questionnaire and educational lesson (the song) will be translated into *Tshivenda* and *Xitsonga*, which are the local language spoken in Musina and Collins Chabane municipalities. Experts from the MER Centre for African languages at the University of Venda will carry this exercise. One expert will translate the questionnaire from English to *Tshivenda* and *Xitsonga* and another expert from the same department will translate the *Tshivenda* and *Xitsonga* version of the questionnaire back to English.

1. ***Data analysis***

Demographic, environmental, dietary diversity score, FFQ, zinc and iron data will be captured on the spreadsheet excel for further statistical analysis using SPSS version 24 or latest. Means, frequencies, chi-square, median and interquartile range, Pearson’s correlation and regression analysis will be used for descriptive statistics.

